### **Visit 2 (end of period 2)**

Visit 2 will entail the following procedures:

- Acquisition of the data download from the closed-loop system
- Acquisition of the data download from the SNAQ app (control group only)
- Feedback questionnaire on the SNAQ app (control group only)

At the end of the visit and throughout period 3, participants of the control group will undergo a period of 3 weeks without using the SNAQ app. The license for using the SNAQ app will be temporarily de-activated remotely.

### **Visit 3 (control group only)**

Visit 3 will entail the following procedures:

- Acquisition of the data downloads (data from the closed-loop system and the SNAQ app)

After the last visit (Visit 2 for participants of the intervention group and Visit 3 for the control group) participants will continue to have free access to the premium version of the SNAQ app. Participants will not receive instructions on how to use the app during this period. Data on SNAQ app use during this period will be collected at the end of the period. At the end of this period, the study will be terminated and the study phones (if applicable) will be collected.

During the whole study duration, all participants will continue to use their usual diabetes therapy (including hybrid-closed loop system and the type of insulin). The study will not specify nor change any aspects related to the participants' insulin treatment settings. Whenever possible, the participant should not change their diabetes therapy during the course of the study due to the potential of confounding effects.

## **Methods**

### *Sensor glucose control, insulin dose and treatment settings*

For each study period, sensor glucose, insulin data and treatment settings will be self-downloaded by the participants, de-identified (by replacing identifiable information by the assigned study ID) and shared with the study team. After checking that all data is de-identified, the study team will store the files as source data in the REDCap study base. Raw data will be further processed in R using custom scripts to calculate outcomes based on sensor glucose and insulin data. All signals will be resampled at 5 minutes intervals before further processing using linear interpolation. Sensor glucose gaps up to 20 minutes will be interpolated (gaps larger than 20 minutes will be discarded for the calculation of sensor glucose control). All calculated variables will be entered into the study database.

Following variables will be calculated or retrieved:

- Total daily insulin dose (daily basal and bolus dose, number of manual boluses)
- Carbohydrate (g/U), insulin sensitivity factors (mmol/L/U), active insulin time (h), glucose target (mmol/L)
- Sensor glucose control (time in target range, time in hypoglycaemia (time < 3.0mmol/L, time < 3.9 mmol/L, time between 3.1-3.9 mmol/L), time in hyperglycaemia (time > 10.0 mmol/L, time > 13.9 mmol/L, time between 10.1-13.9 mmol/L, time > 20.0 mmol/L), postprandial time in target range, postprandial time in hypoglycaemia (time < 3.0mmol/L and time < 3.9 mmol/L, time between 3.1-3.9 mmol/L), postprandial time in hyperglycaemia (time > 10.0 mmol/L, time > 13.9 mmol/L, time between 10.1-13.9 mmol/L, time > 20.0 mmol/L), mean sensor glucose, SD of sensor glucose, CV of sensor glucose)

### *Dietary intake*

Daily frequency and mean daily amount and timing of macronutrient intake (carbohydrate, protein, fat) will be calculated from the download of the SNAQ app. Information on carbohydrate intake will be additionally calculated from data of the hybrid closed-loop system (carbohydrates entered by the participants in their closed-loop systems).

### *Nutrition literacy, meal management and feedback questionnaires*

Nutrition literacy will be expressed as mean signed and absolute relative errors (%) of carbohydrate error and be calculated over all items of the quiz on a subject level. The nutrition literacy, the meal management and the feedback questionnaire will be implemented in the survey tool of the RedCap platform and can be completed remotely using a participant specific link.

### *Usability/Usefulness*

The frequency of SNAQ app use will be calculated for the applicable study periods. Further objective information on the usability of the SNAQ app will be evaluated by assessing the manual corrections of the segmentation, food recognition and proposed meal macronutrient content. All data will be retrieved from the SNAQ app. The System Usability Scale will be filled by the participants after the intervention to assess the usability of the app as part of the feedback questionnaire.

## **3.4 Withdrawal and discontinuation**

Subjects will be withdrawn from the investigation under the following circumstances

- The subject's behavior interferes with a safe conduct of the study
- Decision by the treating clinical team that termination is in the subject's best medical interest
- Decision by the Sponsor-investigator that termination is in the subjects' best medical interest
- The subject wishes to terminate the study
- Pregnancy during the study period, as confirmed by a positive urine-pregnancy test (beta-hCG elevation over test-specific threshold).

Participants who are withdrawn from the study will not be replaced. Reasons for withdrawal (if indicated) will be documented. In case of withdrawal upon subject request, all collected data remains coded, as indicated in Informed Consent document. Efforts will be made to follow the subject up for the primary endpoint assessment even if the intervention is discontinued. Due to the nature of the study no exit survey/examination will be performed in participants who discontinue the participation in the study prior to the final visit unless for safety reasons.

## **3.5 Randomization**

Eligible participants will be randomly allocated (1:1) to the intervention group or the control group. Group allocation will be done according to an adaptive stratified randomization framework using the minimization method, implemented in the MinimPy randomisation software to balance between group characteristics. The following minimisation factors will be considered: glycated haemoglobin A1C ( $<7.5$  or  $\geq 7.5$  %), sex, time in target range (3.9-10.0mmol/L) in the 14 days prior to the study inclusion ( $>75\%$  or  $<75\%$ ).

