### 3 STUDY POPULATION AND STUDY PROCEDURES

#### 3.1 Inclusion and exclusion criteria, justification of study population

Subjects fulfilling all of the following inclusion criteria are eligible for the investigation:

- Written informed consent
- Adults (aged 18 years or older)
- Type 1 diabetes (as defined by World Health Organization-WHO for at least 12 month)
- Current use of a commercial hybrid closed-loop system
- HbA1c ≤ 12% (measured within the past 3 months)
- Willing to use the SNAQ app on a daily basis for over 3 weeks
- The participant is willing to follow study specific instructions and share their treatment data with the study team

The presence of any of the following exclusion criteria will lead to the exclusion of the subject

- Any physical or psychological disease or condition likely to interfere with the normal conduct of the study and interpretation of the study results
- Previous use of SNAQ app for more than 5 days within the past 3 months
- Self-reported pregnancy, planned pregnancy within next 3 months or breast-feeding
- Severe visual impairment
- Severe hearing impairment
- Lack of reliable telephone facility for contact
- Concomitant participation in another trial that interferes with the normal conduct of the study and interpretation of the study results
- Participant not proficient in German

*Comment:*

- 1) *The exclusion of pregnant and breastfeeding participants is not due to potential safety issues but due to concerns regarding interpretation of study results (impact of pregnancy on physiology, psychometrics and behaviour patterns).*
- 2) *If the last measurement of HbA1c levels is older than 3 months, a new measurement of HbA1c will be performed if the participant consents to that, if not, the participant will be excluded.*

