#### 3.2 Recruitment, screening and informed consent procedure

Participants will be recruited from the adult diabetes outpatient clinics at the University Hospital Bern or from referring clinicians working at other outpatient clinics. Potential participants will be identified by their treating clinicians. If agreed by the participants, their contact details will be shared with the research team who will approach them to provide further details about the study, both written and spoken. Specifically, the investigators will explain to each interested individual the nature of the study, its purpose, the procedures involved, the expected duration, the potential risks and benefits and any discomfort it may entail. Each participant will be informed that the participation in the study is voluntary and that he or she may withdraw from the study at any time and that withdrawal of consent will not affect his or her subsequent medical assistance and treatment. Participants will also be informed that there will be no reimbursement for the

participation in this investigation and that authorised individuals other than their treating physician may examine his/her medical records.

A study information sheet, which also contains the consent form, will be send out to the potential participants. Any questions from the subject or its related persons shall be addressed. Enough time will be given to the participant to decide whether to participate or not. Written consent will be obtained after the provision of a minimum of 24h of reflection time.

If continued interest exists and participants appear eligible, participants will be asked to sign the consent form and return it to the investigators before or on the day of the arranged baseline visit. The Sponsor-Investigator or its designate will sign the returned document before the commencement of the baseline visit and ask the participant whether a copy is desired. The participants will not be submitted to any study-related procedure before obtaining written informed consent. The signed consent form will be retained as part of the study records. The informed consent process will be documented in the patient file and any discrepancy to the process described in the protocol will be explained.

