**Figure 1. Study Flow**

#### Baseline visit

The baseline visit will include the following procedure

- Retrieval of relevant medical information
- Questionnaire exploring the participants' current meal management practices, perceived importance and related burden
- Nutrition literacy questionnaire

In order to assess people's baseline glucose control and insulin requirements, participants will be asked to download their data from the hybrid closed-loop systems from the 14 preceding days and share them with the study team.

The following details will be recorded in the eCRF to characterize the population:

- Sociodemographic and anthropometrics variables (age, gender, body weight, height, level of education, socioeconomic status)
- Diabetes-specific medical details: age at diagnosis, duration of diabetes, type of commercial hybrid closed-loop system, type of insulin, diabetes-related complications
- Comorbidities
- Medications other than insulin (glucose lowering agents, lipid lowering agents, anti-hypertensive agents)
- History of severe hypoglycaemia and hypoglycaemia awareness status (Gold score)

All recorded parameters including units and scales are defined in the case report form.

In participants without a smartphone compatible with the newest version of SNAQ app, a study phone will be provided to the patients for the duration of the study. In addition, all participants will be provided with the premium version of SNAQ app for 12 months (including 6 weeks of the study and excluding the period when the usage of the app is not intended regarding the participation group) by using a specific code.

After completion of all baseline assessments participants will be randomized to the intervention or the control group. Participants of the intervention group will be asked to use SNAQ app for 3 weeks while in participants in the control group no instructions of any kind will be made by the study team. Before the use of the SNAQ app, participants of the intervention group will receive access to the premium version of the app using a specific code, assistance with the download of the app, registration with the assigned study ID and a short guidance through the app given by the team, using the informational material provided by SNAQ app.

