## **7.3 Confidentiality and coding**

Trial and participant data will be handled with uttermost discretion and is only accessible to authorised personnel who require the data to fulfil their duties within the scope of the study. On the CRFs and other study specific documents, participants are only identified by a unique study ID.

All collected data will be labelled with the subject ID (composed of the study acronym and a two digit number; e.g. SuMMIT\_01). No biological specimens will be collected. The subject identification list will be kept in the Investigator Site File during the course of the clinical trial. During the study the Sponsor-Investigator has access to all documents of the investigation including randomization lists and coding keys.

After completion or termination of the study, the subject identification list will be kept by a person outside of the study team ([name], Department of Diabetes, Endocrinology Nutritional Medicine and Metabolism, University Hospital Bern). In case of further use of research data, the researchers in charge will not have access to the subject identification list.

Direct access to source documents will be permitted for purposes of monitoring, audits and inspections. The Sponsor-Investigator will declare who will have access to the documents of the investigation, dataset, randomization code, etc. during and after the investigation.

The study data base in REDCap® can only be accessed by designated investigator staff entering a username and password. The application has a group and role-based security model. Each user belongs to one or more security groups with specific sets of permissions about folder or projects in the system. Only dedicated site administrators have access to the admin console, enabling user management and changing security settings.

All events are recorded in the user event list of the audit log files. Data are stored and visualised in data grids either in the format of datasets, lists or assays. Each change of data is tracked and documented in corresponding audit log files.

The servers are behind a firewall and cannot be accessed through the internet. They are located in locked dedicated server rooms with restricted access. Apache HTTP Server and REDCap® were configured to run under Secure Sockets Layer (SSL) which implies that data is encrypted and transmitted securely.

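### Minimisation with no stated random element, a randomisation list open to the Sponsor-Investigator and no separation of allocation from enrolment make the next arm predictable well above chance

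*Protocol*

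**What the plan says.** Protocol section 3.5 states that "Eligible participants will be randomly allocated (1:1) to the intervention group or the control group", and that this is done "using the minimization method, implemented in the MinimPy randomisation software to balance between group characteristics". There are three factors, each with two levels: HbA1c (cut at 7.5%), sex, and "time in target range (3.9-10.0mmol/L) in the 14 days prior to the study inclusion" (cut at 75%). The section gives no probability for the balancing arm, no imbalance measure, no weights and no tie rule.

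On timing, section 3.3 (Baseline visit) says "After completion of all baseline assessments participants will be randomized to the intervention or the control group". Appendix 1 places eligibility screening at screening and again at the baseline visit, which is also where randomisation takes place. One exclusion criterion in section 3.1 calls for judgement: "Any physical or psychological disease or condition likely to interfere with the normal conduct of the study and interpretation of the study results".

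On people, section 3.2 has the research team approach candidates after the treating clinicians identify them. For the consent form, "The Sponsor-Investigator or its designate will sign the returned document before the commencement of the baseline visit". Section 7.3 then states: "During the study the Sponsor-Investigator has access to all documents of the investigation including randomization lists and coding keys". It adds that the Sponsor-Investigator will declare who else may see the randomisation code and other documents.

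The comparison is app use against no instruction, so each participant's arm is visible to the team.

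**The concern.** Minimisation has no schedule of future assignments to hide. The next arm depends on the earlier allocations, with their factor levels, and on the new participant's own levels. The running list is therefore what a person needs to predict the next arm. Section 7.3 grants that list, during recruitment, to the role whose team recruits. This is a written access rule, so the point does not rest on missing detail alone.

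At the baseline visit the factors are in hand while acceptance is still open under a criterion that needs judgement. If acceptance or deferral leans on the expected arm, even unconsciously, the groups can differ in traits outside the three factors, such as motivation or expected engagement with an app. Adjusting for baseline time in range does not remove such differences. In an unmasked trial, concealing the next assignment is a safeguard that can still be kept.

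**Working it through.** **1. The plan's own figures.** Section 4.1 uses a difference of 10 points, SD 10, two-sided 5% and 80% power. A two-sample t-test gives n = 16.7, so 17 per group (power 80.7%). Then 17 / (1 − 0.20) = 21.25, so 22 per group and 44 in total. Both figures reproduce. The protocol gives no figure for predictability.

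**2. Inputs to the predictability check.** From the protocol: 44 participants, 1:1 allocation, three two-level factors. Assumed, because the protocol is silent: equal weights; ties broken 50:50; independent factors with prevalences 0.5/0.5/0.5 or 0.3/0.4/0.6; imbalance measured as the sum of absolute or of squared marginal differences; and probability p of assigning the balancing arm.

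**3. Rule.** For each factor f, let D_f be the number in the app arm minus the number in the control arm among earlier participants who share the new participant's level. With the absolute measure, the score is Σ|D_f + 1| for the app arm and Σ|D_f − 1| for control. The lower score marks the preferred arm, which is assigned with probability p. For a guesser who holds the list and the factors:

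share correct = (share with a preferred arm) × p + (share tied) × 0.5

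Absolute measure, prevalences 0.5:
- p = 1: 0.762 × 1 + 0.238 × 0.5 = 0.881
- p = 0.95: 0.768 × 0.95 + 0.232 × 0.5 = 0.846
- p = 0.8: 0.790 × 0.8 + 0.210 × 0.5 = 0.737
- p = 0.7: 0.810 × 0.7 + 0.190 × 0.5 = 0.662

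**4. Results over both measures and both sets of prevalences.**

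| p | Correct, list and three factors | Correct, overall arm totals only |
|---|---|---|
| 1 | 88-89% | about 71% |
| 0.95 | 85-86% | about 70% |
| 0.9 | 81-83% | about 68% |
| 0.8 | 74-75% | about 64% |
| 0.7 | 66-68% | about 60% |

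Chance is 50%. At p = 1, 76-78% of assignments are fully determined in advance. At any p below 1, none is.

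**5. Before the baseline download.** Time in range comes with the data download at the baseline visit, but sex and HbA1c (an eligibility item) are known earlier. With the list and those two factors only, correct guesses are about 81% at p = 1, 75% at p = 0.9 and 68-69% at p = 0.8.

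**6. What a bias could do (illustrative only).** Assume an outcome SD of 10, an enroller's impression that correlates r with the outcome, and deferral of a share q of candidates whose predicted arm does not suit. None of r, q or the deferral itself has a source in the protocol. Simulated bias b under deterministic minimisation was converted to a type I error with a noncentral t, where the noncentrality is b / (10 × √(2/n)). For b = 2 and n = 22 it is 2 / (10 × 0.3015) = 0.66.

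| r, q | Bias (points) | Type I error, 17 to 22 per group |
|---|---|---|
| 0.3, 0.25 | 0.55 | 5.3-5.4% |
| 0.5, 0.25 | 0.81 | 5.6-5.8% |
| 0.3, 0.5 | 1.22 | 6.4-6.8% |
| 0.5, 0.5 | 1.98 | 8.7-9.8% |

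At p = 0.8 the same four scenarios give 0.33, 0.51, 0.70 and 1.17 points. The largest of these corresponds to an error of 6.3-6.7%.

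**The case against.** A reader might infer that most next assignments can be worked out with certainty. The protocol does not support that. Section 3.5 neither states nor excludes a random element, it calls the allocation random, and the setting may be fixed in another document. The 76-78% determined share holds only at p = 1. This part of the objection stands.

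It can also be said that list access adds little, since past arms are visible in an unmasked trial. That does not hold. Knowing how many are in each arm is not the same as holding the factor-by-factor record: 88% against 71% correct at p = 1, and 74% against 64% at p = 0.8. It is true that withholding the list does not restore 50%. It is also true that section 7.3 opens the list by name only to the Sponsor-Investigator and leaves others' access to a later declaration.

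The consent signature comes before the baseline visit and is not an eligibility decision, so full prediction is confined to the interval between the download and randomisation. Yet eligibility is still being checked then, and two factors suffice for a fair guess earlier.

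Other limits on the harm are real. Section 3.2 requires reasons for non-participation and unsuitability to be recorded, the outcome is sensor-derived and baseline-adjusted, and the investigators declare no conflict of interest. These restrain selective enrolment or make it easier to detect; they do not conceal the next arm.

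**Conclusion.** The point holds as one of predictability, not certainty. As written, the protocol lets a role tied to enrolment hold what is needed to predict the next arm: about 88% correct if the minimisation is deterministic, about 66-86% for p of 0.7-0.95. These figures rest on the assumed weights, tie rule and factor prevalences, and they changed little across the measures and prevalences tried.

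The size of any selection bias cannot be derived from the protocol. Three of the four illustrative scenarios leave the type I error below 7%, and only the most extreme reaches 9-10%. A reader might take the 2-point bias as an estimate, or conclude that selective enrolment is expected. Neither follows, because the assumed correlations and deferral rates have no source in the protocol. The case for change is that a plain gap in concealment can be closed at little cost.

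**What to change.** - **Section 7.3:** withhold the randomisation list and the running factor totals from the Sponsor-Investigator and all enrolling staff until the last participant is randomised. Align the sentence on declared access with this.
- **Section 3.5, random element:** state that the minimisation assigns the balancing arm with probability below 1, and keep the exact value in a restricted randomisation document. Printing it in the protocol would give it to those who enrol.
- **Section 3.5, separation:** state that an existing team member with no part in recruitment or eligibility decisions (for example the data manager mentioned in section 7.1) runs MinimPy, and only after consent, eligibility and baseline data are locked.

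Locking eligibility first matters most, because some predictability remains: at p = 0.8, staff who know only the arm totals would still guess about 64% correctly.

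The cost is protocol wording, one software setting and one restricted document. Sample size, visits and analysis do not change. Balance on the three factors becomes slightly looser. For time in range the planned baseline adjustment largely absorbs this; for sex and HbA1c it does so only in so far as they act through baseline time in range.
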